### Covariates

#### Health, cost of healthcare and patient experience

The following potential covariates will be used in analyses on both healthcare claims-based and questionnaire-based data: age, sex, socioeconomic status (based on ecological proxy: postal codes), urbanicity, other comorbidities and proxies for parkinsonism-specific health status. The proxies for parkinsonism-specific health status are operationalized based on years since diagnosis of parkinsonism, parkinsonism specific drugs used ATC code N04 [47], parkinsonism-related complications in the year before enrolment, number of outpatient neurology visits in the year before enrolment, characteristics of the hospital where the majority of the patient’s care is delivered, and number of allied health professional consultations in the year before enrolment [53–59]. For analyses on cost of healthcare, we will additionally adjust for total cost of care in the years prior to the start of this study.

For analyses on questionnaire-based data, we will additionally adjust for: ethnicity, marital status, work status, living situation, urbanicity, age at parkinsonism diagnosis, height and weight, weekly physical activity, smoking, alcohol, caffeine, cognitive performance using a telephone MoCA, complications in the last year, whether a care manager or carer is involved in current care, other comorbidities, and both current and expected quality of care in the participant’s region. Due to the Coronavirus Disease 2019 (COVID-19) crisis in the Netherlands we will also examine the experienced impact of the COVID-19 crisis using a standardized questionnaire about the discomfort that people have experienced due to the COVID-19 pandemic. This 8-item questionnaire describes different situations that may have applied due to COVID-19 related stress. The questionnaire is scored on a 6-point Likert-scale ranging from 0 ('this situation did not occur') to 5 ('very troublesome').

#### Carer experience

The following potential covariates will be used: age, sex, education, marital status, work status, living situation and the carer’s relationship to the patient, as well as patient characteristics.

#### Healthcare professional experience

The following potential covariates will be used: age and sex of the healthcare professional, type of profession, work environment (hospital vs primary care setting), years of experience, number of persons with parkinsonism seen per year by the healthcare professional.

### Statistical analysis

#### Overview

In the next paragraph, we present a global outline and sample size calculation of the primary overall analysis of this study. We intend to separately publish a detailed statistical analysis plan, which will cover -among other items- how the simultaneous occurrence of multiple admissions will be handled, how complications will be weighed, and how the influence of the COVID-19 pandemic will be handled. The detailed statistical analysis plan will also contain our approach and sample size calculations for secondary endpoint analyses, including questionnaire-based analyses.

#### Primary endpoint analysis

We will use a negative binomial regression model in which the difference-in-difference, operationalized as an interaction term between time (pre- or post-implementation of PRIME Parkinson care in selected region) and model of care (PRIME Parkinson care or usual care), is the independent variable of interest and the number of PD-related complications (a count variable) is the dependent variable. All covariates described in the previous section will be entered as fixed effects; additionally, random intercepts and random slopes over time will be included. To handle missing data on potential covariates, we will perform multiple imputation based on age, sex and other potential covariates.

#### Sample size calculation

We estimate that approximately 5% of persons with parkinsonism who receive care at a community hospital in The Netherlands reside in the PRIME Parkinson care region [60]. We estimate that there was no difference between regions in parkinsonism-related complications prior to implementation of PRIME Parkinson care in the selected region, and that -after implementation- PRIME Parkinson care will be associated with a 25% reduction in parkinsonism-related complications compared to usual care. This effect would be slightly higher than the effect of specialized physiotherapy compared to generic physiotherapy in a previous study [53]. In both regions, we expect a similar mortality rate as in the intervention arm of the same previous study (28.9 deaths/1000 person-year)[53] and an emigration rate similar to recent estimates from the Statistics Netherlands (CBS) (9 emigrants/1000 person-year)[61, 62]. Since Vektis has healthcare expenditure-based data on all insured individuals in The Netherlands, we expect attrition due to other causes to be minimal. After correction for expected attrition, we would require a total sample size of 29,990 to have 80% power at alpha 5%. This indicates that the estimated number of persons with parkinsonism in both regions (n ~ 50,000) are more than sufficient to detect a 25% difference in parkinsonism-related complications between regions. Of note, since we have defined a single endpoint for the overall primary analysis of this study, we will not adapt statistical threshold for multiple testing.

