#### Eligibility criteria and definition of regions

Persons with a clinical diagnosis of parkinsonism, except those in whom the cause is medication use (which is potentially reversible), who receive their treatment in a community hospital will be eligible for the study. In this context we refer to non-university medical centres as a community hospital. The PRIME Parkinson care region consists of four community hospitals: Bernhoven Ziekenhuis, Canisius Wilhelmina Ziekenhuis, Maasziekenhuis Pantein, Rijnstate Ziekenhuis. In Fig. 2 the PRIME Parkinson care region is presented visually. Persons who receive parkinsonism treatment in the PRIME Parkinson care region will be compared to persons in a community hospital outside the above-defined region who receive usual care for parkinsonism. There are 60 community hospitals in the usual care region. In both groups, the targeted population is representative of the broad spectrum of persons with parkinsonism who are treated in a community hospital.

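### The power statement names no allowance for clustering, although PRIME care goes to only 4 neighbouring hospitals and the level of the random effects is not stated, so the 80% power is not supported

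*Protocol article*

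**What the plan says.** Under Sample size calculation, the article gives one requirement: "After correction for expected attrition, we would require a total sample size of 29,990 to have 80% power at alpha 5" per cent. The inputs named there are an index share of about 5%, the assumption of "no difference between regions in parkinsonism-related complications prior to implementation of PRIME Parkinson care in the selected region", the expectation that "PRIME Parkinson care will be associated with a 25% reduction in parkinsonism-related complications compared to usual care", 28.9 deaths per 1000 person-years and 9 emigrants per 1000 person-years. It concludes that the estimated 50,000 or so patients "are more than sufficient to detect a 25% difference in parkinsonism-related complications between regions".

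Under Eligibility criteria and definition of regions: "The PRIME Parkinson care region consists of four community hospitals", and "There are 60 community hospitals in the usual care region". The study design overview adds that the four lie within 25 km of one university centre.

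Under Primary endpoint analysis, the model is a negative binomial difference-in-difference with covariates as fixed effects; "additionally, random intercepts and random slopes over time will be included". The grouping level (patient, hospital or region) is not given. Characteristics of the treating hospital are among the listed covariates.

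**The concern.** The type of care a patient receives is set by hospital, within one region. A difference-in-difference removes stable differences between hospitals. It does not remove differences in how hospitals change from the pre- to the post-implementation period. That hospital-by-period variance enters the contrast divided by 4 on the index side, and adding patients to those 4 hospitals cannot reduce it. A patient total alone therefore cannot show that the design is large enough.

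Two things are at stake for the single primary endpoint. Power may be lower than stated. And if the random effects describe patients only, ordinary drift in four hospitals can be read as an effect of PRIME care more often than 5% of the time.

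**Working it through.** **Reproducing 29,990.** It cannot be rebuilt, because the complication rate and the negative binomial dispersion are not given. It is compatible with a patient-level calculation: for example, a Poisson comparison of the post-implementation period alone needs a control mean of about 0.09 to 0.10 complications per person over the attrition periods tried. That neither confirms nor refutes the figure. The check below instead takes 29,990 as giving exactly 80% power under independence, two-sided (sidedness is not stated).

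**Inputs from the article.** Rate ratio 0.75; alpha 5%; power 80%; index share 5%, so 29,990 splits into 1,499.5 and 28,490.5; available patients 2,000 and 48,000 (Abstract); 4 and 60 hospitals.

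**Assumed input.** tau, the between-hospital SD of the pre-post change in log rate. The article gives no value, so a range is shown.

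**Step 1: variance implied by the stated power.** |ln 0.75| = 0.2877. Required SE = 0.2877 / (1.960 + 0.842) = 0.1027; variance 0.01054.

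**Step 2: rescale to the available patients.** (1/2,000 + 1/48,000) / (1/1,499.5 + 1/28,490.5) = 0.0005208 / 0.0007020 = 0.742. Variance = 0.742 × 0.01054 = 0.00782; SE 0.0884. Power under independence = Φ(0.2877/0.0884 − 1.96) = 90%.

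**Step 3: add the hospital-by-period term.** Total variance = 0.00782 + tau² × (1/4 + 1/60). Power = Φ(0.2877/SE − 1.96). Type I error of a test that uses only the patient-level SE = 2 × [1 − Φ(1.96 × 0.0884/SE)].

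| tau | Total variance | SE | Power | Type I error, patient-level test |
|---|---|---|---|---|
| 0 | 0.00782 | 0.0884 | 90% | 5% |
| 0.05 | 0.00849 | 0.0921 | 88% | 6% |
| 0.10 | 0.01049 | 0.1024 | 80% | 9% |
| 0.15 | 0.01382 | 0.1176 | 69% | 14% |
| 0.20 | 0.01849 | 0.1360 | 56% | 20% |

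If tau is estimated jointly from all 64 hospitals (t reference, about 62 degrees of freedom), power at tau 0.10, 0.15 and 0.20 is about 79, 67 and 55%, so the choice of reference distribution matters little under this model.

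**Step 4: where the margin ends.** Power reaches 80% when the total variance equals 0.01054: tau = √[(0.01054 − 0.00782) / 0.2667] ≈ 0.10. The sample size section uses a 5% share, whereas 2,000 of 50,000 is 4%. With 5% (2,500 and 47,500), the patient-level variance is 0.00632, power under independence is 95%, and the threshold rises to tau ≈ 0.126. With unlimited patients in these hospitals, 80% still requires tau ≤ √(0.01054 / 0.2667) ≈ 0.20.

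**Step 5: a shock common to the index region.** Hospital terms treat the 4 index hospitals as drifting independently. A region-wide shift with an assumed SD of 0.10 on the log scale adds 0.01 to the variance undivided: at 2,000/48,000, power is 58% and the type I error of a patient-level test is 19%.

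**The case against.** A reader might infer that the calculation treats patients as independent, that the 80% claim is false, and that the planned test is anti-conservative. The document supports none of these outright.

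- The absence of a clustering allowance is read from the list of stated inputs. Because 29,990 cannot be rebuilt, an unstated allowance cannot be excluded.
- Every loss of power above depends on an assumed tau. Stable hospital differences cancel, 50,000 leaves a margin over 29,990, and power stays at or above 80% up to tau of about 0.10, or about 0.126 with the 5% share.
- A patient-level test is not what the plan says; it gives no level. Random slopes over time at hospital level would absorb much of the hospital-specific change.
- The authors have not ignored regional drift. The Discussion concedes that the controlled before-after comparison does not handle confounding that varies over time and by area, and adds 2019 claims. Hospital characteristics and prior complications are adjusted for.
- The section is called a global outline, with a detailed analysis plan to follow.

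These points stand as limits on the wording, but they do not remove the concern. The Overview of the statistical analysis presents the primary sample size here and defers sample sizes only for secondary endpoints, so the sufficiency conclusion is this article's own. Covariates and an extra pre-implementation year do not supply a standard error for differential change. The Discussion itself reports marked regional differences in COVID-19 incidence as baseline assessments were due to start in 2020, so a zero region-by-period effect cannot be taken for granted. Either reading of the random effects leaves a gap: at patient level the test can be too liberal; at hospital level the standard error includes a component for which the sample size section names no allowance.

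**Conclusion.** The point holds as a lack of support, not as proof of error. The sufficiency claim rests on a count of patients, while the number of treated hospitals is 4, and no between-hospital variance of change is stated. A tau of about 0.10, roughly a 10% hospital-level variation in the pre-post change, uses up the whole margin between 29,990 and the 2,000/48,000 available; at 0.20 power is 56%. The inflated type I error (6 to 20% over tau 0.05 to 0.20) applies only if the random effects sit at patient level alone. All figures rest on the calibration to 80% at 29,990, a two-sided test, a normal approximation and an assumed tau.

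**What to change.** 1. State the level of the random effects. Put a hospital random intercept and a hospital-by-period random effect in the primary model alongside the patient effect.
2. Prespecify inference suited to few treated clusters. One option is permutation: assign the PRIME label to sets of 4 neighbouring control hospitals and compare the observed difference-in-difference with that distribution. This need not be the sole primary inference, but it should be at least a prespecified check, because hospital terms alone do not cover a shock common to the one index region.
3. Replace the 29,990 and sufficiency statement with power over a range of tau, estimated from pre-2021 claims of the control hospitals. State the complication rate, the dispersion and one index share (4% or 5%).

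Cost: analysis-plan wording and some programming. The interval will be wider and the stated power less favourable. No extra patients are needed.

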## Discussion

In this prospective clinical cohort study we will determine the utility of PRIME Parkinson care in the Netherlands, which is a novel integrated care approach for persons with parkinsonism, their carers and the healthcare professionals who are involved in their care. We will also include an economic evaluation. There are several methodological issues related to the study design that need to be considered. First, given the essential role of regional collaboration in PRIME Parkinson care in the Netherlands, we did not consider it feasible to randomize the type of care to clusters at a hospital level. Therefore, PRIME Parkinson care was not introduced as a research intervention in the index region but rather as a replacement of usual care, and the nature of the evaluation of the utility of the model is observational. Any observed differences on outcomes may therefore reflect confounding by other regional factors be they operating at an individual or structural level. We will attempt to adjust for these factors in our multivariable models. The controlled before and after comparison will also adjust for unmeasured confounding unless they vary over time and by area. In other settings where regional collaboration is already well-developed as part of usual care, a clustered randomized controlled trial may be feasible. Second, we have chosen to include only persons with parkinsonism from non-academic centres in the evaluation of the utility of PRIME Parkinson care. The reason for this choice is that usual care for persons with parkinsonism in community hospitals in the PRIME Parkinson care region is likely reflective of usual care in community hospitals across The Netherlands. By contrast, usual care for persons with parkinsonism at Radboud University Medical Centre, which is a tertiary movement disorder centre, is less reflective of usual care for persons with parkinsonism at other academic centres, with the possible exception of other tertiary movement disorder centres. Third, recruitment strategies are identical across the PRIME Parkinson care and usual care regions, with one exception: treating neurologists in the PRIME Parkinson care region will inform persons with parkinsonism of the possibility of participating in a questionnaire-based evaluation of regional differences in the quality of care. This additional recruitment activity could introduce selection bias if they disproportionally attracted participants prone to an accelerated -or, conversely, decelerated- decline in health. To quantify possible selection bias that may arise because of this difference in recruitment, we will assess differences between regions in the baseline characteristics of participants. Fourth, shortly before the planned initiation of baseline assessments for persons with parkinsonism, carers and healthcare professionals in the spring of 2020, the COVID-19 crisis erupted in The Netherlands, with profound regional differences in the incidence of COVID-19 [63]. We employed several complementary strategies to carefully measure how the COVID-19 crisis may have influenced the evaluation of the model, and adjust for that influence as much as possible. In the questionnaire-based study, we added a questionnaire on the impact of the COVID-19 crisis experienced by persons with parkinsonism, carers and healthcare providers. This questionnaire will allow us to quantify potential confounding or information bias that may arise if there are regional differences in the impact of the COVID-19 crisis. Furthermore, we added a questionnaire to measure whether uptake of some elements of the model was accelerated by the COVID-19 crisis, such as the use of telemedicine tools that allow for a shift of care closer to home. Such an accelerated uptake would be in line with the international experience, suggesting that telemedicine tools such as videoconferencing have been adopted more readily than in the years before [64]. Despite these precautionary measures that we have taken, it remains possible that the COVID-19 crisis may have had residual effects on the 2020 baseline evaluation that are not directly measurable through questionnaires. To further mitigate the possible effects of this confounding influence, we intend to perform a difference-in-difference analysis of outcomes in the PRIME Parkinson care and usual care regions over time, instead of relying on a single baseline measurement, in both the questionnaire-based and insurance claims-based study. For the latter, we will also include data from 2019.

We also consider several issues regarding the external validity of this study. First, since the PRIME Parkinson care model will be administered to persons with PD as well as to persons with atypical parkinsonism, this evaluation will also include both diagnostic categories. As a consequence, we expect results of this study to be largely generalisable to persons with parkinsonism irrespective of their underlying diagnosis. Second, we have chosen to include persons with parkinsonism (and carers) at all stages of parkinsonism, to allow for a sample that is representative of the population of persons with parkinsonism in a community hospital. An inherent consequence of this design is that specific subgroups of persons with parkinsonism who are less prone to frequent outpatient visits, e.g. people who do not have capacity to consent to the study or who have developed cognitive problems or persons living in a nursing home, may be relatively underrepresented across both study arms. The results arising from the PRIME Parkinson care model in the Netherlands will be compared to parallel – but independently acquired – results from the United Kingdom (Bath area). Assuming that the findings across both studies will be consistent, this will provide greater certainty that the underlying model behind PRIME Parkinson has validity and is generalisable to different high-income populations, despite differences in health care systems as well as cultural differences across both regions. The primary analysis of the evaluation of the model in each country will be separate, as some elements in the implementation of the model may differ between The Netherlands and the United Kingdom because of different needs in the current respective healthcare systems. Still, in secondary analyses, we intend to learn from the utility of the model in these heterogeneous settings, in order to enhance the external validity of results.

Further details about PRIME Parkinson care in the United Kingdom (PRIME-UK) will be forthcoming and we publish a prespecified analysis plan combining the Dutch and United Kingdom outcomes where appropriate, which will also yield increased statistical power for the assessment of differences between specific subgroups.

We believe that empirical insight on the potential utility of PRIME Parkinson care may be generalisable to other disorders, as parkinsonism can be regarded as a “model condition” for many other chronic neurological disorders, given its wide-ranging clinical phenotype, involvement of multiple professional disciplines in care, multimodal management (e.g., pharmacotherapy, neurosurgical procedures), the long disease duration, and relatively high prevalence [12]. Furthermore, we hypothesize that due to the proactive and collaborative nature of PRIME Parkinson care, persons will be empowered to function better with parkinsonism, leading to improvements in health and patient experience of care -as well as beneficially affecting carer experience and healthcare professional wellbeing- while maintaining cost neutrality. Should this hypothesis be confirmed, then a financial model for this novel care package will have to be developed to demonstrate sustainability and facilitate possible dissemination and implementation to other regions and other high income countries.

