## Methods

### Overview of study design and data sources

This is a prospective observational study, which will run from January 1, 2020 through December 31, 2023. The study comprises two data sources: healthcare claims-based data and questionnaire-based data. We will use healthcare claims-based data to compare all persons with parkinsonism in the PRIME Parkinson care region (Index sample) with all persons with parkinsonism across other regions in The Netherlands (Control sample). The choice to include four community hospitals in the PRIME Parkinson care region was determined by the available funding. The choice for these specific hospitals was based on their geographical proximity (i.e., a 25 km radius) to the Radboud University Medical Centre, as well as a prior history of collaboration in clinical and research settings [20, 21].

Furthermore, we will perform annual questionnaire-based assessments in a subsample which will be approximately equally divided over the PRIME Parkinson care and usual care regions (estimated numbers: 1,200 persons with parkinsonism, 600 caregivers and 250 healthcare providers). Since PRIME Parkinson care will be implemented in the Index region from January 1, 2021 onwards, we consider the first year (January 1, 2020 through December 31, 2020) as the baseline observational period and the following three years (January 1, 2021 through December 31, 2023) as the implementation period. An overview of the patient study population is provided in Fig. 1.

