#### Questionnaire-based data

Participants will self-administer questionnaires electronically, with the exception of the telephone Montreal Cognitive Assessment (MoCA) which will be conducted over the phone for all participants. Participants who are not able to complete electronic questionnaires will be provided with two alternatives: paper-based self-administration or telephone-based interview administration. We will conduct annual assessments between 2020 and 2023, i.e. one baseline and three follow-up assessments at 12, 24 and 36 months after enrolment.

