#### Recruitment process in the questionnaire-based study

The recruitment of persons with parkinsonism comprises three phases: actively informing potential participants (phase 1), providing additional information to those who are interested (phase 2), and obtaining informed consent (phase 3).

Phase 1 entails publicising the study through various channels. First, invitation letters will be sent to members of ParkinsonNEXT, a web-based platform for persons with parkinsonism and their carers who have expressed an interest in participating in research. Second, the Parkinson Vereniging (Dutch Parkinson patient association) will send newsletters and share posts on their website. Third, a brochure with a reply card has been designed that will be shared with potential participants at different events organized for persons with parkinsonism or their carers, including -among others- ParkinsonNEXT innovation and research events and the national ParkinsonNet congress. One additional recruitment strategy will be applied in the PRIME Parkinson care region only, to increase the likelihood that the target sample size in that region will be reached: hospital-based neurologists in the PRIME Parkinson care region will send information letters to all persons with parkinsonism affiliated to their hospital.

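### Neurologist letters in the PRIME region only may select questionnaire participants on rate of decline, and the planned baseline comparison can flag gross imbalance but cannot quantify that bias

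*Protocol article*

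**What the plan says.** The section on recruitment for the questionnaire-based study lists channels open to both regions: the research platform, the patient association, and brochures at events. It then adds: "One additional recruitment strategy will be applied in the PRIME Parkinson care region only". Under this strategy, "hospital-based neurologists in the PRIME Parkinson care region will send information letters to all persons with parkinsonism affiliated to their hospital". Carers are recruited in almost the same way, and also through participating patients.

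The design overview gives the size of the questionnaire subsample ("estimated numbers: 1,200 persons with parkinsonism, 600 caregivers and 250 healthcare providers"), which is to be "approximately equally divided over the PRIME Parkinson care and usual care regions". Each participant has "one baseline and three follow-up assessments at 12, 24 and 36 months after enrolment". No one is enrolled after the baseline round.

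The Discussion accepts that the extra channel could introduce "selection bias if they disproportionally attracted participants prone to an accelerated -or, conversely, decelerated- decline in health". Its stated response is: "To quantify possible selection bias that may arise because of this difference in recruitment, we will assess differences between regions in the baseline characteristics". The same section plans a difference-in-difference analysis for both the questionnaire and the claims data, as a safeguard against COVID-19 effects, and adds 2019 data for the claims study only.

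**The concern.** The article identifies the right threat and pairs it with a check of a different kind. The threat is that participants reached by letter follow a different course after enrolment. The check is a comparison of the two regional samples at enrolment.

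A difference-in-difference removes a fixed difference in level between regions. It does not remove a difference in slope, and the Discussion itself grants that confounding which differs by area and changes over time remains. Selection on slope through a channel used in one region is of exactly that type. It would appear in the PRIME estimate as benefit or harm, depending on its direction.

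What is at stake is the reading of the patient and carer questionnaire results, most directly the health measures such as the PDQ-39. A reassuring baseline table would be taken as evidence that the recruitment difference did no damage, because the article says that this table measures it.

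**Working it through.** **No figure to reproduce.** The article's sample size of 29,990 concerns the claims-based primary endpoint. Sample sizes for the questionnaire analyses are left to a separate analysis plan. The numbers below are therefore illustrations, and every input that the article does not give is marked as an assumption.

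**Inputs from the article.** 1,200 patients split about equally, so about 600 per region; one wave before implementation; follow-up at 1, 2 and 3 years.

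**Step 1: what enters the estimate.** Let common-route participants have mean annual change *m* in both regions. Let letter-recruited participants have *m* + δ, and let them form a share *p* of the PRIME-region sample. At year *T*:

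- PRIME-region change = (*m* + *p*δ)*T* + care effect
- usual-care change = *mT*
- difference-in-difference = care effect + *p*δ*T*

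Baseline levels cancel, and the bias *p*δ*T* remains. With δ = 1 point a year (assumption):

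| Share by letter (assumption) | Averaged over years 1, 2, 3 (mean *T* = 2) | At 36 months (*T* = 3) |
|---|---|---|
| 0.25 | 0.50 | 0.75 |
| 0.50 | 1.00 | 1.50 |
| 0.75 | 1.50 | 2.25 |

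The figures scale in proportion to δ, and their sign follows that of δ.

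**Step 2: what the baseline check sees.** Suppose mean slopes differ between regions by *d* slope-SDs, and a baseline characteristic correlates *r* with slope (assumptions). The expected baseline difference is *r* × *d* SD. With 600 per region its standard error is √(2/600) = 0.0577 SD, so 80% power needs a difference of (1.96 + 0.84) × 0.0577 = 0.16 SD. The chance of flagging a difference is about Φ(*rd*/0.0577 − 1.96), or the nominal 5% at *r* = 0. For *d* = 0.2:

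| *r* | Expected baseline difference (SD) | Chance that it is flagged |
|---|---|---|
| 0 | 0 | 5% |
| 0.2 | 0.04 | 10% |
| 0.3 | 0.06 | 18% |
| 0.5 | 0.10 | 41% |

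**Step 3: what the difference-in-difference does meanwhile.** Let slope and residual each contribute an SD of 0.5 to the change score (assumption), with no true care effect. At *d* = 0.2 the expected bias is 0.5 × 0.2 = 0.10 SD. Its standard error is √(0.25 + 0.25) × 0.0577 = 0.041, so the chance of a false significant result is about Φ(0.10/0.041 − 1.96) = Φ(0.48), or 68 to 69%. A simulation of 2,000 runs per scenario gave 70% at *r* = 0 and 67% at *r* = 0.3, while the baseline check flagged imbalance in 5% and 18% of runs. Over *d* = 0.1 to 0.3, false significance ran from about 22% to 95%, and flagging from 5% to 34%.

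**Step 4: whether adjustment rescues it.** Regressing the change on the baseline variable at *r* = 0.3 reduced the simulated bias from 0.099 to 0.090. That agrees with a remaining fraction of 1 − *r*² = 0.91.

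**Step 5: why a flagged difference still does not quantify the bias.** The observed baseline difference is *rd* plus any true difference in level between the regional populations. Neither *r* nor that true difference is known, and with one wave before implementation the questionnaire data hold no earlier slope from which to learn *d*.

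**The case against.** **The baseline data are rich.** Listed covariates and outcomes include years since diagnosis, age at diagnosis, telephone MoCA, complications in the last year, antiparkinsonian drugs, and motor and autonomic scales. Severity relative to disease duration is a crude marker of past progression. Step 2 models one variable, not this set taken together. This stands: gross selection could be noticed. A reader might infer that the baseline comparison is useless, and the article does not support that. What it lacks is any means of turning an imbalance into an amount of bias.

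**The questionnaire analyses will be adjusted.** This stands in part. How much adjustment helps depends on a model that the article does not give, for example on whether covariates may act on change over time. If the remaining fraction in step 4 carries over to several covariates, they would need to explain half of the variation in slope to halve the bias.

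**Analysis by route belongs to the analysis plan.** Agreed, and its absence from the article is not the point. The article itself commits to a baseline comparison as the way to quantify this bias, and that statement is wrong as written.

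**The scope is limited.** This stands fully. A reader might infer that the study's main result is at risk. It is not: the primary endpoint and costs come from claims data on all patients, and consent applies only to the questionnaires. Healthcare professionals are invited through a professional network with no region-specific channel stated. For a measure of care experience such as the PACIC+, the link from decline in health to the score needs a further step that the article does not supply.

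**Route-based analyses are imperfect too.** This also stands. Route differences over time within the PRIME region arise under PRIME care, whose uptake is expected to be incomplete, so they mix natural course with uptake and response. They cannot serve as the measure of selection.

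**Conclusion.** The concern holds for the patient and carer questionnaire endpoints. The letters may select on rate of decline, in either direction. The between-region baseline comparison can show gross imbalance through partial markers, but it cannot quantify a difference in slope, because there is a single wave before implementation and recruitment route is mixed with region.

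The article does not show that selection on slope will occur, nor how large it would be. The 1.0 point averaged over follow-up and 1.5 points at 36 months rest wholly on an assumed 50% letter share and an assumed difference of 1 point a year. The simulated error rates rest on assumed slope differences of 0.1 to 0.3 SD. Neither should be read as an estimate of the bias in this study. They show only that a material bias and an unremarkable baseline table can occur together.

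The point is worth correcting because the correction is cheap. It does not threaten the overall primary analysis.

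**What to change.** 1. Record the recruitment route for every patient and carer at enrolment. If enrolment has closed, ask at the next annual assessment and accept some recall error.
2. Pre-specify a sensitivity analysis of the patient and carer questionnaire endpoints, restricted to participants who joined through routes used in both regions.
3. Report baseline and trajectory differences by route within the PRIME region as descriptive only, and say that they also reflect uptake of and response to PRIME care.
4. Reword the Discussion so that the baseline comparison describes imbalance between the regional samples and is not said to quantify selection bias.

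The cost is one data field, one further analysis and one sentence. There are two drawbacks. The restricted analysis has fewer PRIME-region participants and so less precision. That restricted group may also be altered, because the letters go to all patients of the hospitals concerned, including some who would otherwise have joined by a shared route. It is therefore a sensitivity analysis, not a replacement for the main questionnaire analysis.
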